## Abstract

The impact of dementia on caregivers is complex and multi-dimensional. In low- and middle-income settings, caregivers are often left without adequate support, despite their multiple needs. These include health information, caregiving skills, social and emotional support, and access to local resources—all of which can be partially fulfilled by technology. In recent years, mobile apps have emerged and proven useful for caregivers. We found a few existing apps suitable for Malaysian users in terms of affordability and cultural and linguistic compatibility. Our study aims to design a mobile app that suits dementia caregivers in Malaysia and consists of three phases. Phase I is content development that employs Focus Group Discussion (FGD) and Nominal Group Technique (NGT) involving field experts. Phase II comprises a mobile app (Demensia KITA) designed in collaboration with a software developer specializing in mobile health apps. Phase III entails testing the usability of the app using the Malay version of the mHealth App Usability Questionnaire (M-MAUQ). This study protocol elaborates on the rigorous steps of designing a mobile app and testing its usability, along with anticipated challenges. Our protocol will provide insight for future researchers, healthcare providers, and policymakers and pave the way for better use of digital technology in the field of aging and caregiving.

## 1. Introduction

### 1.1. Background

Most people living with dementia (PLwD) are in low- and middle-income (LMIC) countries [1,2], posing a great economic burden to these nations [1,2,3]. Worldwide, dementia has resulted in disability and reliance among older persons [2]. In the context of developing regions, family members are the most common caregivers for dementia patients regardless of their disease stage [4]. Dementia is a general term for memory, thinking, and decision-making impairment that interferes with daily activities, and is not always part of normal aging [5]. Dementia affects approximately 7% of adults aged 60 and older [2,6]. Globally, the number of individuals aged 60 or over is expected to reach 1.4 billion by 2030, and nearly 2.1 billion by 2050 [7]. This rapid increase in older populations could indicate an upward trend in dementia prevalence. Currently, in Asia, the pooled prevalence of all-type dementia for people over 60 years old is 3299 per 10,000 people [8], and the number is expected to rise further by 2030 [2]. In Malaysia, the prevalence of dementia among older adults in 2018 stood at 8.5% [9]. 

There is a general lack of awareness and understanding of dementia, resulting in stigma and barriers to diagnosis and treatment [2]. PLwD typically has concurrent health problems, such as diabetes mellitus and vascular-related diseases [10], which complicate their treatment and lead to high costs of healthcare [3,10]. Dementia brings physical, psychological, social, and economic consequences that affect not only people living with dementia (PLwD) but also their caregivers, families, and society. Studies found that informal caregivers (e.g., family members) spent an overwhelming average of five hours a day caring for people with dementia [2] and are more vulnerable to mental disorders such as depression [11]. This could be attributed to factors such as the lack of a support system, high caregiving strain, insufficient coping skills, inability to access local resources, care recipient behavioral problems, economic burden due to direct medical and non-medical costs, as well as potential income losses [3,12]. 

In recent years, digital technology has become part and parcel of health and the healthcare system, including in the geriatric and caregiving fields. For instance, mobile applications (more commonly known as mobile apps) could improve public health [13] as they have become more visible and popular as tools for disseminating health information, connecting users with surrounding resources, and healthcare delivery [14]. In addition, prior studies showed that mobile assistive apps could improve the quality of life (QOL) for PLwD by assisting with tasks and encouraging independence, thus alleviating the caregiving burden [15,16,17]. 

Similarly, access to smartphones and other smart devices has grown exponentially across the globe. In 2018, it was estimated that 83% of adults in developing countries worldwide owned a smartphone [18]. In the same year, Malaysia had 17.2 million smartphone users, with a forecast of over 21 million by 2023 [19,20]. Given that the ownership of a smart device is not restricted to the upper-income groups [20], mobile apps that are used for health-related purposes have the potential to reach caregivers from underserved and marginalized populations [21]. Furthermore, the recent COVID-19 pandemic has boosted the use of mobile health apps [22], and more people worldwide are increasingly using apps to improve their health either by accessing information or utilizing health-related services [23,24,25]. 

### 1.2. Study Rationale

Evidence shows that many mobile apps developed for healthcare intervention and health improvements are highly effective [26,27,28,29]. Similarly, most dementia care mobile apps have been demonstrated to improve the QOL of PLwD and their caregivers and reduce caregiver burden [30,31,32]. Since the QOL of PLwD is intricately bounded to the QOL of their caregivers, apps that target caregivers as users are critical to strengthening dementia care in the community. Nevertheless, existing mobile apps for dementia are mostly developed in high-income regions [30,31,32,33] and, therefore, primarily and originally intended for their populations. In addition, more of these apps are designed for PLwD [34,35,36] instead of caregivers. As a result, while having excellent features, these apps are often not socio-culturally compatible with users or caregivers in other settings. For instance, existing apps tend to be in the English language [32,34,35,36,37], some incur high charges for services offered [21,32,38], and do not include aspects of caregiving that are unique to the local customs or social norms [38]. Thus, it is difficult to find a mobile app that meets the needs of PLwD caregivers in a specific context, in the low- and middle-income region [31,33]. Our in-depth literature review on dementia caregiving and existing mobile apps for PLwD caregivers identified a need for an app to support caregivers in the Malaysian context. 

### 1.3. Research Objectives

The general aim of this study is to develop and assess the usability of “Demensia KITA”, a mobile app for dementia caregivers in Malaysia. Specific objectives include:To develop suitable and relevant content for the mobile application.To develop and design a mobile app prototype that uses the national language (Bahasa Malaysia) as the interface.To determine the usability of the mobile app among PLwD caregivers.

## 2. Methodology

### Study Design

This research employs a combination of qualitative and quantitative methods and comprises three phases. In Phase I, Focus Group Discussion (FGD) and Nominal Group Technique (NGT) will be used to develop the app content. In Phase II, the mobile app is developed and designed. In Phase III, the usability of the app is tested using the Malay version of the mHealth App Usability Questionnaire (M-MAUQ). 

**Phase I: Establishment of an expert committee for developing the app content.**

Firstly, an expert committee consisting of geriatricians, geriatric psychiatrists, occupational therapists, dietitians, dentists, nurses, and caregivers will be established. These various types of expertise were determined based on discussions with two public health experts and a geriatric psychiatrist from Universiti Teknologi MARA (UiTM), who have previously worked on several dementia-related projects. This phase is expected to take approximately three months to complete. The main objective is to gather and discuss the relevant content that should be included in the app. This will be conducted using FGDs among the experts, and NGT among the PLwD caregivers. The NGT will be conducted first to gather information about the needs of PLwD caregivers and later communicate that knowledge to the group of experts.

**1.** 
**Nominal Group Technique (NGT)**

In this study, NGT is aimed at PLwD caregivers. NGT refers to a structured variation of a small-group discussion to achieve consensus from the target groups most closely related to the area of concern. It involves four steps: generating, recording, discussing, and voting on ideas [39]. Depending on the participant’s availability, NGT will be conducted face-to-face or online using video conference platforms, such as Google Meet [40].

**NGT sampling and selection criteria:**

While NGT has been conducted with groups of between 2 and 14 people, a limit of seven has been recommended [41,42]. Seven caregivers of PLwD will be purposively selected from two tertiary healthcare institutions in Malaysia: University Malaya Medical Centre (UMMC) and General Hospital Kuala Lumpur (GHKL), as they serve a greater number of PLwD than other institutions in Malaysia and have well-established multidisciplinary teams for the management of PLwD. To ensure the groups’ generalizability, different caregivers from diverse backgrounds will be selected (i.e., different social statuses, different age groups, different education levels, and different ethnicity). Individuals who have not consented and are not able to communicate independently in English or Malay language will be excluded from the study. The following criteria apply to NGT participants:

Inclusion criteria for caregivers:

Primary caregiver of a person living with mild dementia. A primary caregiver is defined as a person who helps in the personal care of an older adult with dementia, regardless of their education or experience, for one month or more, in the last 12 months [43,44].Aged ≥ 18 years old.Primary caregiver of a dependent person aged ≥ 60 years old diagnosed with any form of dementia.

All participants will be briefed about the NGT approach. First, the moderator will deliver the questions or problems to the group (in written form) and read them. She will then instruct everyone to write down their thoughts in short phrases or statements, discreetly and independently for 20 min [41]. Second, members of the group give each other comments in a round-robin approach without debate at this point. An idea from a group member is written on a whiteboard or chart visible to the whole group, and this process will continue until all points are recorded. Third, each idea is discussed for clarity and relevance. This stage allows group members to convey their feedback and opinion regarding the idea given in terms of rationale and value. Fourth, each person will rank the compiled ideas privately, then vote to determine which points should be prioritized. An example to illustrate this process is as follows: each group member selects five items from the group list and writes one on a card or paper. Next, each member ranks the five ideas, with the most important receiving a score of 5 and the least important receiving a score of 1 [45]. Examples are shown in Table 1:

Next is the determination of the NGT threshold, which refers to the value of the NGT score above which solution is considered relevant and should be prioritized for execution [45]. Generally, the NGT threshold should be half the maximum of the NGT score [45]. In the preceding example, the maximum possible NGT score of 5 × 5 is 25. The NGT threshold is half the maximum attainable NGT score (12.5) or scores equal to or above 13. Therefore, solutions or ideas 1, 3, 4, and 5 should be prioritized for implementation. 

For an online NGT, participants will be informed beforehand of their roles, as traditional procedural parts of meetings have been limited by screen-based engagement [40]. The group will be given approximately 30 min to ensure that everyone has an opportunity to practice utilizing the virtual platform. A similar method will then be used, except that when group members generate ideas, they will write them down on a piece of paper and show them on screen or read them out loud, while the moderator records their ideas on a PowerPoint presentation shared with everyone in real time.

**2.** 
**Focus Group Discussion (FGD)**

FGD is a group interview with approximately 6 to 12 individuals who share similar qualities or interests. This technique is beneficial for acquiring quicker, in-depth insight into a subject that is more difficult to understand (or acquire data) using other methods [46]. The FGD involves field experts going through a series of topics to exchange ideas and points of view, aiming to reach a consensus on app themes and appropriate content [46]. Findings from the NGT sessions will be discussed with FGD participants. FGD participants will consist of geriatricians, geriatric psychiatrists, occupational therapists, nurses, dietitians, and dentists. At least one member from each specialty will be identified and recruited to ensure diverse experiences and perspectives.

The FGD will be conducted face-to-face or via an online platform, depending on the circumstances and participants’ preferences [46]. If it is conducted online, all participants will first be briefed about the FGD approach, the session objectives, and the anticipated outcome. This step will take approximately 90 min [46]. Next, the facilitator will pose questions to the group and allow members to respond to each other’s views. Once consensus is reached, the moderator will compile all relevant information, summarize the findings, and communicate them to the expert committee for final approval. The content will then be converted into a format that suits a mobile app. 

**Phase II: Designing of “Demensia KITA”**

Phase II will begin upon completion of phase I. It will entail designing and developing the mobile app, named “Demensia KITA”, with a software developer from within academia specializing in health-related mobile apps.

The preliminary prototype in this phase will be a native mobile application [47] optimized for a specific device and operating system and can be downloaded and installed from a web store (Play Store). It will be free of charge at this stage. Android will be selected as the mobile operating system due to its global dominance [48]. Apart from appropriate typography [49], the prototype aims to incorporate four primary features: rich experience; intuitive; personalized experience; and simplicity [50]. According to Forbes, 14% of smartphone users delete an app that is difficult to use [50]. As a result, easy navigation and overall usability, such as fewer clicks and actions, will be considered to ensure a positive mobile app user experience. The user interface will be as straightforward and intuitive as possible. The prototype version of the mobile app will also function offline, potentially extending reach to underserved populations as internet access is only required for app downloading and software updating. 

Demensia KITA will be fully operated in *Bahasa Malaysia*. The registration process will be personalized and simplified, and users will be able to log in using their personal external accounts such as Google, Facebook, and Twitter. Apart from credible information regarding dementia care, there will be features such as relevant spiritual and cultural practices to keep caregivers motivated and engaged.

Phase II is expected to take approximately one year. The early prototype version will be registered for a one-time fee on Google’s Android (Google Play Store) operating system platform to evaluate its usability. The Alpha version (an early pre-release version that is part of a dedicated testing process) [51] will be tested among 30 dementia caregivers conveniently selected from GHKL and UMMC beforehand to ensure the functionality of the app.

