**Study setting**

Phase III will be conducted at the Geriatric Department of UMMC and the Memory Clinic of GHKL. The estimated time frame is approximately three months.

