**Study population and sampling procedure**

The target population in this phase is PLwD caregivers. We will recruit caregivers of PLwD who attend regular follow-ups at UMMC and GHKL. Prior to recruitment, the researcher will contact the healthcare staff at the selected institutions to estimate the total number of patients and their caregivers. If the amount is large enough to allow random sampling, this method will be done to select respondents. However, convenient sampling may be employed if the number is too small to allow for adequate probability sampling. The inclusion and exclusion criteria for caregivers are presented in Table 2.

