Of equal importance is mobile app sustainability in the long run, which again, needs to be part of the study plan. Engaging with a credible mobile app developer is one way of ensuring the utility and longevity of the app, but this requires balancing with other issues like ensuring affordable access and data privacy protection. Collaborations with private or business entities have their own merit but at times can get rather complicated for researchers to handle. In such cases, it is wise for the researcher to obtain legal advice from the legal unit of the academic institution or find alternatives, such as partnering with non-profit entities or software developers from within the academia. 

Another challenge is improving the generalizability of Phase III findings. If the study population is small—meaning the number of PLwD and their caregivers is not practically adequate to allow for a random selection—we may have to employ convenient sampling. However, this method is susceptible to selection bias, as the caregivers selected may not represent the whole caregiver population. To address this issue, universal sampling can be done. Alternatively, we can take additional steps to ensure a diverse sample regarding sociodemographic characteristics (e.g., age, race, education level, and location (urban or rural). 

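### The Phase III eligibility rule lets caregivers who shaped or Alpha-tested the app return as its usability raters, so the score may not be an independent rating by new users

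*Protocol article*

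**What the plan says.** Caregivers from two hospitals, UMMC and GHKL, enter the study at several points.

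- **Phase I, NGT sampling and selection criteria:** "Seven caregivers of PLwD will be purposively selected from two tertiary healthcare institutions in Malaysia", which are then named as UMMC and GHKL. These caregivers generate and rank the needs that are passed to the experts.
- **Phase I, expert committee:** "an expert committee consisting of geriatricians, geriatric psychiatrists, occupational therapists, dietitians, dentists, nurses, and caregivers will be established". The number and source of the committee's caregivers are not stated.
- **Phase II, designing of the app:** the Alpha version "will be tested among 30 dementia caregivers conveniently selected from GHKL and UMMC beforehand to ensure the functionality of the app". The Beta version follows once the Alpha version has been corrected.
- **Phase III, study setting:** "Phase III will be conducted at the Geriatric Department of UMMC and the Memory Clinic of GHKL".
- **Phase III, study population and sampling procedure:** "We will recruit caregivers of PLwD who attend regular follow-ups at UMMC and GHKL". Random sampling is used if the pool is large enough; otherwise "convenient sampling may be employed if the number is too small to allow for adequate probability sampling".
- **Table 2 (Phase III eligibility):** there are two exclusions, inability to communicate in English or Malay and not using Android. Earlier participation is not mentioned.
- **Discussion:** on the selection bias of convenience sampling, "To address this issue, universal sampling can be done"; a deliberately diverse sample is the alternative.

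The Phase III result is a single-group mean M-MAUQ total, read against a fixed cut-off of 72 on a scale from 18 to 126.

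**The concern.** Phase III has no comparator, so the meaning of its result depends on who does the rating. The article defines ease of use through the effort of understanding, learning and operating the app. Someone who has worked through the Alpha version has already spent part of that effort. Someone who helped set the content, or whose fault reports were acted on, is not a detached judge of usefulness or satisfaction.

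The eligibility rule does not keep these people apart from new users, and the article plans neither separate samples nor an analysis without earlier participants. Its discussion of selection bias covers representativeness and the urban setting, but not reuse of participants. Overlap is most likely in the situation the plan itself foresees: a small pool and a convenience sample, in which caregivers already known to the team are the easiest to approach. If earlier participation is not recorded, no later analysis can separate the two groups.

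**Working it through.** **Inputs from the article:** NGT caregivers 7; Alpha testers 30; M-MAUQ items 18; sample-to-item ratio 5:1; non-response 20%; cut-off 72.

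**The plan's own figures.** 18 × 5 = 90 needed, and 90 × 1.2 = 108 invited. Both agree with the sample size section.

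**Who could re-enter.** The NGT criteria largely fit inside Table 2. Table 2 adds an Android phone with mobile data and basic smartphone skills, and it speaks of an older relative where the NGT criteria speak of a dependent person. The app is built for Android, so Alpha testers are likely to meet the phone criteria. Most earlier participants could therefore qualify, but the article does not show that all would.

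**Ceiling on overlap** (earlier participants ÷ 90):

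- NGT alone: 7/90 = 7.8%
- Alpha alone: 30/90 = 33.3%
- Both, if no one was in both: 37/90 = 41.1%

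Committee caregivers would add to this, but their number is not given.

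**Shift in the mean total.** Shift = share × 18 × d, where d is the extra score per item among earlier participants. The article gives no value for d, so 0.25 to 1.5 is my assumption.

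| d per item | 10 of 90 | 30 of 90 | 37 of 90 | New-user mean that still reaches 72 at 37 of 90 |
|---|---|---|---|---|
| 0.25 | 0.5 | 1.5 | 1.85 | 70.15 |
| 0.5 | 1.0 | 3.0 | 3.7 | 68.3 |
| 1.0 | 2.0 | 6.0 | 7.4 | 64.6 |
| 1.5 | 3.0 | 9.0 | 11.1 | 60.9 |

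Example: 37/90 × 18 × 0.5 = 3.7, and 72 − 3.7 = 68.3.

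**Under random sampling.** Expected number of earlier participants among 108 invited = 37 × 108 / M, where M is the number of eligible caregivers (assumed, as the article gives none) and all 37 are among them. With equal response, the expected share is 37/M.

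| Pool M | Expected among 108 | Share | Shift for d = 0.25 to 1.5 |
|---|---|---|---|
| 150 | 26.6 | 24.7% | 1.1 to 6.7 |
| 300 | 13.3 | 12.3% | 0.6 to 3.3 |
| 1000 | 4.0 | 3.7% | 0.2 to 1.0 |

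The problem therefore matters mainly when the pool is small. Inviting everyone does not solve it: universal sampling without an exclusion brings in every earlier participant still in follow-up.

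**The case against.** The strongest reply is that the article nowhere says earlier participants will be invited again, and that bias needs both actual overlap and a consistent score difference. That stands. A reader might infer that the score is biased upward as a matter of fact. The documents do not support this, and a tester annoyed by faults in the Alpha version could score lower.

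A reader might also take 41% as the expected overlap. It is only a ceiling. Phase II lasts about a year, so an NGT member would still have to be caring for a patient in follow-up and own a suitable phone. Random sampling is the plan's first choice, and with a large pool it would leave few earlier participants.

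Every Phase III respondent uses the app for four to six weeks before rating it, which narrows the gap in familiarity. NGT ideas also pass a voting threshold and expert review, so members need not see their own requests built in. Both points reduce the likely difference, but neither makes a contributor an independent rater.

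Phase III is partly formative, since its findings feed further changes before the final prototype. This limits the consequence. Even so, the plan attaches a pass mark to the score, and that is the figure readers will use.

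On sampling, it would be too strong to say that the methods prescribe convenience sampling: they permit it, and the Discussion already offers universal sampling. Nor are the same clinics shown to be involved throughout. The NGT and Alpha texts name hospitals; departments are named only for Phase III.

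One might finally say that a fuller protocol would settle this. But Table 2 is presented as the Phase III eligibility criteria, and as written it admits these caregivers.

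**Conclusion.** The point holds as a weakness in the stated eligibility rule, not as a demonstrated bias. The NGT, the Alpha test and Phase III draw on the same two hospitals, and Table 2 allows earlier participants to become Phase III raters. If they do, the mean is not an independent rating by new users and may be biased. Upward is the likelier direction, but this is inference from their familiarity with the app and their part in its content.

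At the ceiling of 37 of 90, the shift is 1.85 to 11.1 points under the assumed 0.25 to 1.5 points per item. It would change the conclusion only if the new-user mean lay below 72 by no more than the shift. Under random sampling from an assumed pool of 1000, the shift is at most about 1 point. It is worth correcting before recruitment because the change is small and an unrecorded overlap cannot be undone afterwards.

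**What to change.** 1. **Table 2, Exclusion.** Add: took part in the Phase I NGT or expert committee, or in the Phase II Alpha test.
2. **If the remaining pool cannot supply 90.** Admit earlier participants, record their earlier participation at enrolment, and make the score without them the primary result, with the score for all respondents reported beside it.
3. **Study population and sampling procedure (secondary).** Where the pool is too small for random selection, replace convenience sampling with the universal sampling already named in the Discussion. Make this change only together with item 1 or item 2.

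**Cost.** One exclusion line and one or two sentences. The pool shrinks by at most 37 caregivers plus any committee caregivers. In a small pool this can matter: an assumed 120 would fall to 120 − 37 = 83, below the required 90. Item 2 is meant for that case, at the price of a primary result based on fewer than 90 respondents.
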